### Inclusion criteria

Patients who will undergo either an open radical cystectomy or a robot-assisted radical cystectomy in Catharina Hospital Eindhoven or Antoni van Leeuwenhoek Hospital are eligible for this study. The choice of treatment is at the discretion of the patient and the surgeon.

For study inclusion, the following criteria must be met:1.Patients must be aged ≥18 yr.2.Patients must be able to understand and sign an informed consent form.3.Patients will undergo either an open radical cystectomy or a robot-assisted radical cystectomy in Catharina Hospital Eindhoven or Antoni van Leeuwenhoek hospital.4.Indication for the radical cystectomy must be urothelial cell carcinoma of the bladder.5.Informed consent of the patient must be obtained to gather data and perform observations during surgery.

### Exclusion criteria

No exclusion criteria will be used for this study.

### Recruitment and consent

Informed consent from both patient and OR staff will be obtained, allowing observation of the surgical procedure and collection of patient data.

### Withdrawal of individuals/employees

Both the patient to undergo the surgery and all employees present during the surgery can always withdraw their consent to the use of their personal data/recording of the surgery. The data collected up to the moment of withdrawal of consent and the recording of the surgery will be destroyed after consent has been withdrawn. Consent can be withdrawn up to 6 mo after surgery in order to have the recorded surgery destroyed. After 6 mo, the recorded surgery will be automatically destroyed.

### Centre details

Based on prior data, on average a total of 35 open radical cystectomies are performed yearly in the Catharina Hospital Eindhoven. Since the robot-assisted radical cystectomy has just been introduced, the total number of open radical cystectomies will be divided over the open radical cystectomy and the robot-assisted radical cystectomy modalities; it is expected that half of the radical cystectomies will be performed using a robot–assisted surgical approach. In the Antoni van Leeuwenhoek Hospital, on average a total of 50 robot-assisted radical cystectomies and 50 open radical cystectomies are performed each year. It is possible to include further hospitals in the future.

## Protocol overview

Patient results will be obtained prospectively. Pathology results will be registered as well as complications occurring within 90 d following surgery. Complications will be registered according to the Clavien-Dindo system surgery.

### Measurements

Nontechnical skills will be observed using five different methods:1.NOTSS: Nontechnical Skills for Surgeons [16].2.Oxford NOTECHS II: a modified theatre team nontechnical skills scoring system [11], [12].3.OTAS: Observational Teamwork Assessment for Surgery [21].4.ICARS: evaluation of nontechnical skills in robotic surgery [17].5.Analysis of human factors [22].

No intracorporeal videos of open radical cystectomy can be recorded due to blocking of the image by the surgeons and the OR lights, and difficulty getting a clear view into the surgical area in the pelvic region from a distance. The analysis of technical skills will be performed only using the robot-assisted radical prostatectomy videos. This method of analysis will be performed to investigate the influence of robot-assisted surgery experience on nontechnical skills and outcome of the surgery. Technical skills in robot-assisted radical cystectomy will be analysed using two different methods:1.GEARS: Global Evaluative Assessment of Robotic Skill [7].2.GERT: Generic Error Rating Tool [5].

### Data collection and handling

Data collection will consist of video capturing and analysis of patient records. Two trained observers (observer 1 and 2, both have a background in medicine), with orientation and training in both nontechnical skills and technical assessment methods, will independently observe surgical videos. All videos will be analysed by both researchers. In case of disagreement, a third independent expert with a psychology and leadership assessment background (observer 3) will be asked to perform a third analysis. Inter-rater reliability will be analysed using Cohen's kappa.

The surgical video will be assessed in multiple phases; in each phase, a nontechnical skills assessment method will be used to assess nontechnical skills. Surgical videos will be analysed using customisable video analysis software “Digital Video Coach” developed by ZEAL IT, Einhoven, The Netherlands (Fig. 2).

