**Fig. 2 fig0010:**
[figure not shown]
Overview of the video analysis software Digital Video Coach.

The video analysis software “Digital Video Coach” makes it possible to register the occurrence of nontechnical skills behaviour and perioperative events (ie, people entering or leaving the OR, phone calls, etc.) Two sets of labels will be created in order to define the different nontechnical skills behaviour and perioperative events present during the surgery. The selection of one of the labels automatically marks the time code corresponding to the moment the label was pressed. This makes it possible to measure the duration of the nontechnical skills behaviour and perioperative events. The labels used for this analysis will be specific to the assessment method of nontechnical skills.

Training of the two observers (observers 1 and 2) will be performed using the NOTSS introductory course and advanced course (NOTSS for Trainees and NOTSS in a Box) as developed by the Royal College of Surgeons of Edinburgh [23]. Further training in the remaining analysis methods will be provided by a specialist in the assessment of nontechnical skills (observer 3).

The technical skills assessment training will be provided by an expert in technical skills analysis with proficient knowledge of the procedure and robot-assisted surgery (observer 4, who is a surgeon who has performed over 200 open radical cystectomy and robot-assisted radical cystectomy procedures and is a trainer of new and experienced surgeons). Observer 4 will act as independent expert in case of disagreement between the two observers (observers 1 and 2).

The videos will be recorded using three cameras installed at three different points in the OR. Objects that should be in view are the OR table, robot console in case of robot-assisted surgery, anaesthesiology equipment, OR door to the nonsterile area of the OR complex, and OR door to the sterile area of the OR. Recording from three different angles in the OR will ensure that there will be a 360° view of the proceedings in the OR. The cameras used have a 170° image angle with high-definition imaging so that maximum coverage can be achieved.

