## Statistical analysis

Frequency statistics will be calculated for patient demographical data, and a Shapiro-Wilk test with *p* > 0.05 will be used to define normal distribution. Univariate analysis will be conducted to test for statistically significant differences in observation scores between open radical cystectomy and robot-assisted radical cystectomy cohorts across all variables, using independent sample *t* tests and Mann-Whitney *U* testing, as appropriate. A variable-selection strategy will be used to create multivariate models. Binary logistic regression will be conducted to calculate odds ratios and 95% confidence intervals for significant predictors on univariate analysis and clinically relevant covariates. Statistical significance is set at *p* < 0.05 based on a two-tailed comparison. Statistical analyses will be performed using SPSS Statistics version 24 (IBM, Armonk, New York, USA).

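### Cohen's kappa, with no weighting stated, is the only agreement measure named for graded scores and durations; in its usual form it would understate the reliability of the primary measurements

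*Protocol article*

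**What the plan says.** Under Data collection and handling, two trained observers rate the recordings independently: "All videos will be analysed by both researchers". Agreement is covered by one sentence: "Inter-rater reliability will be analysed using Cohen's kappa". Weighting is not mentioned, and no second agreement measure is named for any instrument.

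The ratings are of more than one kind.

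- **Graded scores.** The Statistical analysis section states: "Univariate analysis will be conducted to test for statistically significant differences in observation scores between open radical cystectomy" and robot-assisted cohorts, by t test or Mann-Whitney U. Both tests treat the scores as at least ordered.
- **Labels, counts and durations.** The text with Fig. 2 says that the software can "register the occurrence of nontechnical skills behaviour and perioperative events". Each label press stores a time code, and the stated purpose includes measuring how long behaviours and events last.

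On differences between the two raters, the article says: "In case of disagreement, a third independent expert" (observer 3) "will be asked to perform a third analysis". Observer 4 has the corresponding role in the paragraph on technical skills.

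**The concern.** Unweighted kappa is built for nominal categories. It credits exact matches only, so on an ordered scale two observers who are one point apart count as disagreeing as much as two observers at opposite ends. The more levels a scale has, the fewer exact matches there are and the lower kappa falls, even if the observers rank and separate the operations well. A duration has no categories to match, so kappa does not apply to it.

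The observer ratings are the primary outcomes, and the Introduction cites advice to use several trained observers so that inter-observer reliability can be quantified. At stake is whether the reported reliability describes the measurements. A reader shown a kappa of 0.3 or 0.4 would conclude that the tools or the training had failed when the observers may in fact agree well.

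**Working it through.** The article gives no expected kappa, agreement rate or sample size, so there is no stated figure to reproduce. The check asks what each statistic would report for the same pair of raters.

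**Inputs**

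- From the article: two raters, every video rated by both, scores treated as graded, kappa without weighting.
- Assumed: each rater's latent score is standard normal; the latent correlation between raters (ICC) is 0.80; scores are cut into 4, 5 or 8 ordered levels of equal width between −2 and +2 SD, with open end categories.

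**Formulas**

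- Unweighted: kappa = (po − pe) / (1 − pe), where po is observed exact agreement and pe is the exact agreement expected by chance.
- Quadratic-weighted: kappa_w = 1 − Do / De, where Do is the observed and De the chance-expected mean squared difference in levels.

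**Results at latent ICC 0.80**

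| Levels | po | pe | Unweighted kappa | Do | De | Quadratic-weighted kappa |
|---|---|---|---|---|---|---|
| 4 | 0.573 | 0.283 | 0.40 | 0.494 | 1.769 | 0.72 |
| 5 | 0.491 | 0.229 | 0.34 | 0.699 | 2.759 | 0.75 |
| 8 | 0.336 | 0.144 | 0.22 | 1.593 | 7.110 | 0.78 |

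For 5 levels: (0.4906 − 0.2285) / (1 − 0.2285) = 0.2621 / 0.7715 = 0.34, and 1 − 0.699 / 2.759 = 0.75.

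The two statistics move in opposite directions as the scale gets finer. Weighted kappa approaches the latent 0.80, while unweighted kappa falls to about a quarter of it.

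**Sensitivity.** A separate simulation varied how ratings spread over the categories. On a 5-level scale it gave:

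- latent correlation 0.80: unweighted 0.33 to 0.37, quadratic-weighted 0.73 to 0.75;
- latent correlation 0.90: unweighted 0.47 to 0.53, quadratic-weighted 0.83 to 0.86;
- latent correlation 0.95: unweighted 0.59 to 0.67, quadratic-weighted 0.88 to 0.91.

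Quadratic-weighted kappa equalled the two-way ICC to two decimals throughout. Unweighted kappa was the lowest measure in every ordinal setting tried (4, 5, 7 and 8 levels; latent correlation 0.60 to 0.95).

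**The case against.** The best defence is that the weighting is only unstated. Weighted kappa is a recognised form of Cohen's kappa, so the sentence could be read to allow the remedy, and plain kappa does suit the occurrence labels. Part of this stands: kappa is right for nominal labels. But the bare name ordinarily means the unweighted form, it is the only measure named, and no weighting makes it fit durations. Because the article fixes the statistic, a fuller document that is not shown does not dispose of the point.

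A second objection is that a low kappa is only a conservative description. It is correct that kappa alters neither the scores nor the tests applied to them. A reader might infer that every result is undermined; that does not follow.

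A reader might also infer that any difference between the two observers sends the video to a complete third analysis, that nearly every video would go, and that this is unworkable within the six-month storage limit. The article does not say so. It speaks of disagreement and of a third analysis, without stating a threshold, a unit or an extent. The load depends on how that gap is filled:

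- If one difference in any of 17 domains (NOTSS 4, NOTECHS II 4, OTAS 5, ICARS 4) counted, and domains were independent, the share sent would be 1 − 0.80^17 = 98% at 80% exact agreement per domain, 1 − 0.90^17 = 83% at 90%, and 1 − 0.99^17 = 16% at 99%.
- Judged within one four-domain tool, it would be 1 − 0.80^4 = 59% or 1 − 0.90^4 = 34%.
- With correlated differences across 17 domains (within-video correlation 0.1 to 0.3), it would be 43% to 64% at 90%.

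The trigger is therefore undefined rather than wrong, and a condensed article may leave it to a fuller document.

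**Conclusion.** The point holds for the choice of agreement statistic. Kappa in its usual form would report graded ratings as much less reliable than they are: about 0.40, 0.34 and 0.22 on 4-, 5- and 8-level scales, where a measure that respects order gives 0.72 to 0.78. These sizes rest on normal latent scores, a latent ICC of 0.80 and assumed scale lengths. The direction held in every ordinal setting examined, and the gap narrows as true agreement rises. For durations the mismatch needs no assumption.

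The consequence is a misleading account of measurement quality for the primary outcomes, not a bias in the comparison of open with robot-assisted surgery. The documents do not support a claim that the third-rating rule is itself faulty.

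**What to change.** Replace the kappa sentence with a rule by type of data:

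- **Graded scores:** a two-way absolute-agreement ICC, or quadratic-weighted kappa, with a 95% confidence interval, reported per tool.
- **Counts and durations:** the ICC with a 95% confidence interval.
- **Nominal labels:** unweighted kappa, as now.

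State that all of these are computed on the independent ratings of observers 1 and 2, before any third rating by observer 3 or observer 4.

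If a threshold for the third rating is written down, set it per tool. A common margin of more than one scale point would not serve all tools: on an 8-level scale at latent ICC 0.80, two raters fall within one point of each other 77.7% of the time, so with 17 independent domains 1 − 0.777^17 = 99% of videos would still be sent.

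The cost is a change of wording and slightly more analysis, since several agreement measures are reported in place of one. No additional data are needed, provided that the two observers' original ratings are kept.

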**Fig. 2 fig0010:**
[figure not shown]
Overview of the video analysis software Digital Video Coach.

The video analysis software “Digital Video Coach” makes it possible to register the occurrence of nontechnical skills behaviour and perioperative events (ie, people entering or leaving the OR, phone calls, etc.) Two sets of labels will be created in order to define the different nontechnical skills behaviour and perioperative events present during the surgery. The selection of one of the labels automatically marks the time code corresponding to the moment the label was pressed. This makes it possible to measure the duration of the nontechnical skills behaviour and perioperative events. The labels used for this analysis will be specific to the assessment method of nontechnical skills.

Training of the two observers (observers 1 and 2) will be performed using the NOTSS introductory course and advanced course (NOTSS for Trainees and NOTSS in a Box) as developed by the Royal College of Surgeons of Edinburgh [23]. Further training in the remaining analysis methods will be provided by a specialist in the assessment of nontechnical skills (observer 3).

The technical skills assessment training will be provided by an expert in technical skills analysis with proficient knowledge of the procedure and robot-assisted surgery (observer 4, who is a surgeon who has performed over 200 open radical cystectomy and robot-assisted radical cystectomy procedures and is a trainer of new and experienced surgeons). Observer 4 will act as independent expert in case of disagreement between the two observers (observers 1 and 2).

The videos will be recorded using three cameras installed at three different points in the OR. Objects that should be in view are the OR table, robot console in case of robot-assisted surgery, anaesthesiology equipment, OR door to the nonsterile area of the OR complex, and OR door to the sterile area of the OR. Recording from three different angles in the OR will ensure that there will be a 360° view of the proceedings in the OR. The cameras used have a 170° image angle with high-definition imaging so that maximum coverage can be achieved.

Voice data will be collected using personalised voice recorders per staff member present in the OR. The audio feed on the cameras is strong enough to get a general view of the conversations during the surgery; for detailed analysis, recording of the personal voice recorder will be used to gain insight into the orders given during difficult or abnormal phases of the surgery.

Surgeon-specific data will be recorded at the start of the operation, which include but are not limited to the age, gender, right or left handedness, gaming experience, and prior surgical and robot-assisted surgery experience of the surgeon. If multiple surgeons participate in the same surgery, all will be asked to complete the above-mentioned questionnaire; changes in lead surgeon will be recorded during the surgery.

Cases will be deidentified and labelled with study codes. Patient data will be recorded during regular follow-up visits by an oncology nurse or the patient's physician. Since all outcome measures are standard data recorded for these surgeries, no additional strain will be put on the participating patients. This study was granted approval by the institutional medical committee.

Data from the continuous monitoring of the anaesthesiologist are automatically saved in the patients’ medical file. These data will be used to identify the moments when the patient is in distress, that is, a sudden decrease of blood pressure, a sudden increase in heart rate, or a sudden decrease in oxygen saturation of the patient. These moments will be of special interest to the observers in order to observe the reaction of the team to sudden adverse events during surgery.

Data will be handled in a strictly confidential manner, and will be coded during the extraction of either patient characteristics or video analyses. It will be stored in a secure and encrypted database (research manager), and code lists will exclusively be stored at the hospital of consultation or treatment until video analysis results and patient characteristics have been matched. Afterwards, they will be destroyed. The video and audio data will be stored for a maximum period of 6 mo.

## Statistical analysis

Frequency statistics will be calculated for patient demographical data, and a Shapiro-Wilk test with *p* > 0.05 will be used to define normal distribution. Univariate analysis will be conducted to test for statistically significant differences in observation scores between open radical cystectomy and robot-assisted radical cystectomy cohorts across all variables, using independent sample *t* tests and Mann-Whitney *U* testing, as appropriate. A variable-selection strategy will be used to create multivariate models. Binary logistic regression will be conducted to calculate odds ratios and 95% confidence intervals for significant predictors on univariate analysis and clinically relevant covariates. Statistical significance is set at *p* < 0.05 based on a two-tailed comparison. Statistical analyses will be performed using SPSS Statistics version 24 (IBM, Armonk, New York, USA).

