van der Vliet et al [19] advises additional research in nontechnical skills to be performed in different surgical approaches (open, laparoscopic, and robot assisted). Moreover, the use of multiple trained observers is advised for assessing audiovisual recordings of the surgical environment to identify and quantify possible interobserver reliability. The group of Gjeraa et al [18] advises systematic identification of nontechnical skills in minimally invasive surgery in order to develop effective, evidence-based team training programmes for minimally invasive surgeries.

The present study aims to perform a structured evaluation of nontechnical skills in both open and robot-assisted complex surgery, to investigate the manner in which the introduction of a surgical robot influences both nontechnical skills and surgical outcomes during the 1st year of robot-assisted radical cystectomy compared with open radical cystectomy.

In addition, analysis of technical skills in robot-assisted radical cystectomy will be performed to evaluate the possible relationship between technical and nontechnical skills. Radical cystectomy was chosen for this analysis because it is a lengthy, complex, and demanding surgery for the surgeon and other team members.

Since radical cystectomy surgeries take many hours to complete, a long-term and detailed analysis is possible per procedure. Radical cystectomy is traditionally performed using an open surgical approach (open radical cystectomy) at the Catharina Hospital Eindhoven, but recently a shift is made to robot-assisted radical cystectomy. This shift enables us to investigate in which manner nontechnical skills change during the introduction of robot-assisted radical cystectomy. The nontechnical skills during the learning curve of robot-assisted radical cystectomy in the Catharina Hospital Eindhoven will be compared with the nontechnical skills during the open radical cystectomy in the same hospital as well the nontechnical skills of an experienced robot-assisted radical cystectomy team in the Antoni van Leeuwenhoek Hospital.

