### Time scales

The inclusion will be from January 2021 until August 2022 in both hospitals simultaneously (Fig. 1). Video collection will start once the first patient is included and will continue until the last patient has had their surgery. Follow-up data collection will start in February 2021 and will continue until December 2022. Data analysis will start in January 2022.

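### Choosing between t test and Mann-Whitney by a Shapiro-Wilk pre-test lets group size decide whether means or ranks are compared; one prespecified test per score type is better

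*Protocol article*

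**What the plan says.** The Statistical analysis section (same text in the abstract) opens with descriptive statistics for patient demographics. In the same sentence it states that Shapiro-Wilk p > 0.05 "will be used to define normal distribution". The next sentence reads: "Univariate analysis will be conducted to test for statistically significant differences in observation scores between open radical cystectomy and robot-assisted radical cystectomy cohorts", by "independent sample *t* tests and Mann-Whitney *U* testing, as appropriate". The threshold is fixed: "Statistical significance is set at *p* < 0.05 based on a two-tailed comparison". The section does not say whether the t test is the pooled-variance or the Welch form, and it gives no sample size, SD or effect size.

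The Introduction also plans to compare the learning robot team at the Catharina Hospital with open surgery there, "as well the nontechnical skills of an experienced robot-assisted radical cystectomy team in the Antoni van Leeuwenhoek Hospital". The Statistical analysis section names no separate test for that second comparison.

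**The concern.** The only stated criterion that can decide which test is appropriate is the normality pre-test. A pre-test of this kind has little power in small groups and high power in large ones, so the same distribution is called normal in one comparison and non-normal in another. The t test compares means; Mann-Whitney compares ranks. Results for one tool could then refer to different quantities in the Catharina-only and the pooled analyses, and could not be set side by side.

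A second exposure is separate from the pre-test. A pooled t test does not hold its level when group sizes and spreads both differ, and the learning-versus-experienced comparison is expected to be clearly unequal in size. The affected scores are the primary outcomes, and univariate significance also feeds the choice of regression covariates.

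**Working it through.** **Inputs from the protocol article**
- Inclusion period (Time scales): "The inclusion will be from January 2021 until August 2022 in both hospitals simultaneously", that is 20 months.
- Catharina (Centre details): "on average a total of 35 open radical cystectomies are performed yearly in the Catharina Hospital Eindhoven", with half expected to become robot-assisted.
- Antoni van Leeuwenhoek (Centre details): 50 robot-assisted and 50 open per year.
- Two-sided level 0.05.

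The plan states no sample size or power, so there is no figure to reproduce beyond the 5% level.

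**Expected group sizes**
- Catharina robot (learning): 35 × 0.5 × 20/12 = 29.2, about 29; Catharina open the same.
- Antoni van Leeuwenhoek robot (experienced): 50 × 20/12 = 83.3, about 83; open the same.
- Pooled open versus robot: 29 + 83 = 112 in each.

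**Step 1: does group size choose the test?** Share of simulated samples passing Shapiro-Wilk (score shapes assumed):

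| Score | n=10 | n=29 | n=83 | n=112 |
|---|---|---|---|---|
| Sum of four 1-4 items | 80% | 49% | 0% | 0% |
| Mildly skewed (gamma, shape 4) | 86% | 57% | 9% | 2% |

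A second assumed set of item probabilities gave rejection in 16%, 76% and 99% of samples at 29, 83 and 112, that is passes of 84%, 24% and 1%. In a further run of a four-item sum with equal spread, both groups passed in 57% of runs at 29 v 29 and in 0.1% at 112 v 112. The exact rates depend on the assumed shape; the trend does not. A single 1-4 item never passed at n of 20 or more, so for single categories the choice is stable.

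**Step 2: does the pre-test itself inflate error?** With equal means and equal SDs, the two-stage rule at 29 v 83 gave 4.5%-5.3% across all shapes tried. It does not.

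**Step 3: unequal spread at 29 v 83, pooled t test.** Write s1 for the learning and s2 for the experienced SD.
- True variance of the mean difference: V = s1²/29 + s2²/83.
- Variance the pooled test uses: P = [(28·s1² + 82·s2²)/110] × (1/29 + 1/83).
- The nominal critical value of 1.982 acts as 1.982 × √(P/V).

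Results:
- s1/s2 = 1.5: V = 0.0896, P = 0.0613, effective critical value 1.64, normal tail 10.1%.
- s1/s2 = 2: V = 0.1500, P = 0.0821, effective value 1.47, tail 14.3%.
- s2/s1 = 1.5: V = 0.0616, P = 0.0899, effective value 2.39, tail 1.7%.

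Simulation with normal scores (8,000 or 4,000 runs per setting, standard error about 0.2-0.35 points near 5%) agrees:

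| SD ratio | Pre-test, pooled t | Pooled t, no pre-test | Welch, no pre-test |
|---|---|---|---|
| equal | 5.1% | 5.1% | 5.1% |
| learning 1.5 | 10.6% | 10.6% | 5.1% |
| learning 2 | 14.8% | 15.1% | 5.2% |
| experienced 1.5 | 1.8% | 1.7% | 4.8% |

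The second and third columns are nearly identical, so for normal scores the excess comes from pooling the variances.

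**Step 4: discrete totals at 29 v 83.** With summed 1-4 items at SD ratios of about 1.4 and 1.7, the t test was chosen in under 1% of runs and the two-stage rate was 7-8%.

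**Step 5: the balanced open-versus-robot comparison.** Normal and t5 scores stayed at 4.3%-5.4% at every SD ratio, and summed items with equal spread at 112 v 112 gave 5.3%. Only skewed scores with unequal SDs departed: 9%-15% at 29 v 29 and 21%-40% at 112 v 112. That came through the Mann-Whitney branch and counts as error only if the target is a difference in means.

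**Step 6: would Welch inside the two-stage rule be enough?** For normal scores, nearly: 5.2%, 5.8% and 6.1% at ratios 1, 1.5 and 2. For skewed scores with unequal SDs it still gave 14%-22% as a test of means, and for discrete totals about 8%. Welch without the pre-test gave about 4.5%-6.4% for the t5, gamma and lognormal shapes.

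**The case against.** A reader might infer that the Shapiro-Wilk rule pushes false positives above 5% in the learning-versus-experienced comparison. The document does not support that, for five reasons, and all stand:
- With equal spreads the rule holds about 5%. For normal scores, removing the pre-test while keeping the pooled t test changes nothing.
- The pooled form is an assumption; the text says only that independent-sample t tests are used.
- The tests are written for "observation scores between open radical cystectomy and robot-assisted radical cystectomy cohorts across all variables", which are expected to be about equal in size. Their use for learning versus experienced teams is inferred from the Introduction.
- No SD is given, and the direction matters: a more variable experienced team makes the test conservative. The hypothesis of an initial decay makes extra spread in the learning team plausible, but the document does not state or size it.
- The 11-15% belongs to normal scores. Discrete totals would mostly go to Mann-Whitney, where the figure is lower. The article does not say that totals will be formed, and some recorded items are counts or durations.

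It can also be said that the Shapiro-Wilk sentence begins with demographics, so its link to the choice of test is only by adjacency. That is true, but the document offers no other criterion. The form of the t test may fairly be left to a fuller plan; a stated normality threshold followed by a choice of test is a rule already given.

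**Conclusion.** The concern holds in a limited form. As written, group size largely decides whether a summed score is compared by means or by ranks, and this needs no assumption about variances. The pre-test is not shown to raise the error rate by itself, and the open-versus-robot comparison that the section names stays near 5% with normal or summed-item scores.

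The error-rate exposure is conditional. It requires the t test to be the pooled form for the 11-15% figure, the same rule to be carried over to about 29 v 83, and the learning team to be the more variable. The range across the assumptions tried is about 2% to 15% for normal scores and about 8% for discrete totals. This is a cheap improvement, not a defect that undermines the study.

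**What to change.** Delete the Shapiro-Wilk criterion as a way of choosing the test. Name one method per score type and use it in every comparison, including learning versus experienced teams:
- total scores: Welch's t test, reported as a mean difference with 95% interval;
- single-category ratings: one ordinal method, either Mann-Whitney or proportional odds, chosen now.

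The cost is a change of wording. The downside is a negligible loss of power for Welch's test if the variances are in fact equal.
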